### Design

2.2

The project will be conducted with a cluster randomized study design. Each participating forensic mental health in-patient facility will nominate an even number of wards (i.e. clusters of patients), which will then be randomized to either the active (IMR) or control condition (treatment as usual). Randomization of clusters to condition will be matched, in the sense that each participating in-patient facility will have the same number of clusters within the two conditions (e.g. if four wards take part in the study at one facility, two wards will be randomized to each condition). Recruitment of new participating clusters of patients will take place continually until the desired sample size is reached. Assessments of patient outcome measures take place during four different time-points including baseline measurements.

In addition to the patient focused research, the study also aims to explore how staff implementing IMR experience working with the treatment method. This will be done in a mixed-methods fashion, based on the theoretical framework stipulated in Normalization Process Theory [[13], [42]]. Staff working at wards where IMR is implemented will be asked to complete a questionnaire pertaining to aspects of working with the intervention and queried about the same topic in more in-depth qualitative interviews. Data collection from staff will take place at three time-points during the study.

More details on the specifics of data collection is described below, under the heading “Measurement methods”.

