#### Participants and recruitment

2.2.1

We aim to include patients from several forensic mental health inpatient facilities in Sweden. Thus, recruitment will start with approaching the management at the forensic mental health inpatient facility, informing them about the contents of the study and inquiring about their interest in participating. If the decision is made on the clinic level to participate in the study, the representatives of the inpatient facility will be asked to nominate an even number of wards that are considered as comparable to each other as possible. These wards are the clusters of patients that will be randomized to either of the two study conditions. An equal number of wards per inpatient facility will be randomized to either one of the two conditions. In practice, this means that a necessary criterion for each in-patient facility participating in the study is that they have at least two different wards that are considered equal enough in terms of structure and patient characteristics to be comparable to each other. We aim to recruit twelve wards (clusters) for the study (six in each condition) and estimate that a total of 80 patients, 40 in each condition, consent to study participation. To achieve this, we aim to include 4–6 forensic inpatient clinics in the study.

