Prior to randomization of a ward to a specific condition, the patients to subsequently be approached for participation in the study will be identified in cooperation with the clinical team according to the inclusion and exclusion criteria delineated below. After randomization patients fulfilling inclusion criteria at these wards will then be informed about the study and asked for written consent regarding their participation. Recruitment of patients at each ward unit will take place during a time limited window of approximately 3–4 weeks after randomization of the ward unit, before IMR treatment start at wards randomized to the active condition. Given the aforementioned lack of evidence-based interventions in forensic mental health care, we would consider even small effect sizes to be of relevance. With that in mind, we would have preferred a larger sample size to have a sufficiently high probability of discovering such effects. A power calculation conducted in R version 4.1.2. indicated that a total of 228 patients (19 in each cluster) would be needed to achieve 80% power to detect a true effect size of .4, if a small intercluster correlation was presumed. However, it should be noted that some studies of the treatment outcome of IMR have reported substantially higher effect sizes than 0.4 [[16], [40]].

However, the selection of our planned sample size has been made based on a trade-off between a desire for statistical power and pragmatic considerations of what is feasible in a situation of limited time and resources. Furthermore, our study can hopefully be a part of data underlying future meta-analytic studies of the efficacy of treatments within the forensic inpatient context.

In addition to patients participating in the study, staff administering IMR-treatment to patients will also be recruited as participants to the study. These staff participants will answer questions pertaining to their experiences of implementing the intervention. Staff participants will only be recruited from the wards where IMR is implemented. Recruitment of staff participants will take place after the end of staff training prior to treatment commencement. The specific composition of this sample is dependent upon the organization of the wards participating in the study, but it is expected that this will mainly consist of nurses and auxiliary staff. More in-depth inclusion and exclusion criteria both for patient and staff participants are defined below.

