### Data analysis plan

2.4

Comparisons of primary outcome measures between the two conditions will be made on an intention to treat (ITT) basis. Linear mixed modeling (LMM) will be used to assess main effects of time, treatment and time by treatment interactions. A model based on observations nested within subjects, subjects nested within units and units within forensic settings will be evaluated. Models will be compared according to relevant indices of fit, such as AIC, BIC and Log-Likelihood. To test for group differences, post hoc-independent *t*-test will be performed at all time-points. Effect sizes will be expressed in Cohen's d.

In answering the second primary research objective stated above, pertaining to the influence (or non-influence) of potential moderating factors on treatment outcomes, multiple linear regression will be used as an analysis tool.

In regards to the secondary research objective, exploring the experiences of staff administering IMR, a mixed methods approach will be employed. In analyzing quantitative data from the S-NoMAD and change and stability over time on the four indexes of this instrument, linear mixed models will be employed. In analyzing data from the semi-structured interviews with staff, a qualitative approach will be employed.

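### The independent t-tests planned at every time point ignore the randomised wards and the facility matching, so their error rate, including at the primary time point, is not controlled

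*Protocol article*

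**What the plan says.** The Design section makes the ward the unit of randomisation: "Each participating forensic mental health in-patient facility will nominate an even number of wards (i.e. clusters of patients), which will then be randomized". Allocation is balanced by site: "each participating in-patient facility will have the same number of clusters within the two conditions". The planned size is in Participants and recruitment: "We aim to recruit twelve wards (clusters) for the study (six in each condition) and estimate that a total of 80 patients, 40 in each". The same section reports a power calculation that allows for clustering, "if a small intercluster correlation was presumed", but gives no value for that correlation.

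The Data analysis plan has two parts that matter here.

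- A linear mixed model, on an intention-to-treat basis, covers time, treatment and their interaction. Its nesting runs from observations to patients, wards and forensic settings. Candidate models are to be compared on AIC, BIC and log-likelihood.
- Next comes the step for comparing the groups: "To test for group differences, post hoc-independent *t*-test will be performed at all time-points". The section adds "Effect sizes will be expressed in Cohen's d". Nothing links these tests or the effect size to the mixed model, or adjusts them for ward or facility.

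The Outcome measures section and Table 1 define both primary outcomes, the interview WHODAS 2.0 and the HoNOS-S, at treatment completion.

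**The concern.** An independent t-test takes its standard error from the spread between patients, as if about 80 independent people had been randomised. Here 12 wards were. If wards within a facility differ, through their staff, raters or patient mix, the true variance of the difference between conditions exceeds what the test assumes. Balance within facility works the other way: facility differences largely cancel from the comparison but stay in the test's denominator. The unpaired test ignores both, so its actual error rate depends on a variance split that nobody has stated.

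This matters because the primary outcomes are defined at one time point, and the t-test is the only procedure the article names for a group difference at a single time point. A t-test and a mixed model can also disagree at treatment completion, and the article does not say which would decide. Control patients are to be offered IMR if it proves more effective than TAU, and the authors hope that the results will enter meta-analyses. A precision computed as for 80 independent patients would carry into both uses.

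**Working it through.** **Inputs from the article.** 12 wards, 6 per condition; 80 patients, 40 per condition; 80/12 = 6.7 patients per ward; 4 to 6 facilities; allocation balanced within facility. Power calculation: "a total of 228 patients (19 in each cluster) would be needed to achieve 80% power to detect a true effect size of .4".

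**Assumptions.** Two-sided alpha of 0.05 (not stated); intracluster correlation (ICC) 0.01 to 0.10; for the matched cases, 6 facilities with 2 wards each and 7 patients per ward.

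**Step 1: the plan's own figure.** With 114 per arm and 19 per ward, the design effect is 1 + 18 × ICC. Power is Φ(0.4 × √(114 / (2 × design effect)) − 1.96).

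- ICC 0: 85.5%
- ICC 0.008: 80.6%
- ICC 0.009: 80.0%
- ICC 0.01: 79.4%
- ICC 0.02: 73.6%

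So 228 patients is reproduced at an ICC of about 0.009. That value is inferred, not stated, but it shows that the authors planned for the dependence the t-test leaves out.

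**Step 2: error of the t-test under the matched design.** Let f, w and e be the facility, ward and residual variance shares, with f + w + e = 1. Take m = 7 per ward and n = 42 per condition. Apart from the common factor 2/n:

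- true variance of the difference between conditions: e + m × w (facility cancels)
- variance the t-test expects: e + (f + w) × (n − m)/(n − 1) = e + (f + w) × 35/41

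With R the first divided by the second, the approximate error is 2 × (1 − Φ(1.96/√R)).

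| f | w | R | Error, formula | Error, simulated |
|---|---|---|---|---|
| 0 | 0.01 | 1.060/0.999 = 1.06 | 5.7% | 5.7% |
| 0 | 0.05 | 1.300/0.993 = 1.31 | 8.7% | 8.6–8.7% |
| 0 | 0.10 | 1.600/0.985 = 1.62 | 12.4% | 12.1–12.3% |
| 0.025 | 0.025 | 1.125/0.993 = 1.13 | 6.6% | 6.4–6.5% |
| 0.05 | 0.05 | 1.250/0.985 = 1.27 | 8.2% | 8.0–8.2% |
| 0.09 | 0.01 | 0.970/0.985 = 0.98 | 4.8% | 4.8–4.9% |
| 0.05 | 0 | 0.950/0.993 = 0.96 | 4.5% | 4.5–4.6% |
| 0.10 | 0 | 0.900/0.985 = 0.91 | 4.0% | 4.0–4.1% |

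Simulated ranges are over repeated runs; some used the planned 80 patients in wards of 6 or 7. With exactly 80 patients and all correlation between wards, the errors at ICC 0.05 and 0.10 are slightly lower, 8.4% and 12.0%. A t-test on the 12 ward means held 4.9 to 5.2% across ward ICCs of 0 to 0.20.

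**Step 3: precision of Cohen's d.** The naive 95% half-width is 1.99 × √(4/80) = 0.445. Allowing for wards, with all correlation at ward level and 10 degrees of freedom, it is 2.228 × √(4/80 × design effect), where the design effect is 1 + (80/12 − 1) × ICC.

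- ICC 0.01: design effect 1.06, half-width 0.512, ratio to naive 1.15
- ICC 0.05: design effect 1.28, half-width 0.564, ratio 1.27
- ICC 0.10: design effect 1.57, half-width 0.624, ratio 1.40

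**The case against.** The strongest reply is that the planned analysis already respects the clusters. The mixed model nests patients in wards and wards in facilities, and the t-tests are labelled post hoc. This stands in part: the defect is confined to the t-tests, and a reader who concluded that the trial's whole analysis ignores clustering would be wrong. It does not remove the point. The t-tests are the step named for testing group differences, they reach the primary time point, and an independent t-test is not a contrast from the model.

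A second reply concerns size. A reader might infer that the false-positive rate exceeds 5% at any positive ICC. The documents do not support that. Because allocation is balanced within facility, the test is conservative when all clustering lies between facilities. It can stay just below 5% even with some ward variance (4.8 to 4.9% at facility 0.09, ward 0.01). Facilities are also asked to nominate wards as alike as possible, which is meant to keep ward variance down. If the ICC is near the 0.009 implied by the power calculation, the error is at most about 5.7%.

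Third, the article promises no interval for Cohen's d, and the point estimate is little affected by clustering. That is right: only a precision or p-value computed as for independent patients would be wrong.

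Finally, a reader might infer that a baseline comparison has no purpose. Here patients consent after their ward is randomised, so a baseline difference may reflect differential recruitment. The objection is to an unclustered test at baseline, not to looking.

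**Conclusion.** The point holds in this limited form. The article states a test of group differences that disregards both the randomised unit and the matching, and applies it at the time point of both primary outcomes. Its true error against a nominal 5% ranges from about 4% to about 12% over the cases examined, depending on how much variance lies between wards of the same facility. The upper figures need an ICC of 0.10 wholly at ward level; an even split gives about 8%, and a ward ICC of 0.01 gives 5.7%. All of this rests on assumed variance shares, equal wards of 7, six two-ward facilities and two-sided 5% testing. The direction of the error cannot be settled from the article. What can be said is that the rate is not controlled, while the nested model already planned offers a suitable basis for the same comparison. The sentence should be changed before the data are analysed.

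**What to change.** Replace the independent t-tests with IMR minus TAU contrasts at each time point, with 95% confidence intervals, from the planned nested mixed model. In the same edit:

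- Keep the ward and facility terms whatever AIC, BIC or log-likelihood suggest, because they follow from the design.
- Use small-sample degrees of freedom, for example Kenward-Roger.
- Treat baseline either as one of the outcome time points or as a covariate, not both.
- Compute Cohen's d from the model contrast, state the standard deviation used, and give a cluster-adjusted interval.
- Keep any baseline comparison descriptive, or adjust it for clusters.

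The cost is a few sentences and no extra data. Intervals for d become wider than the naive ones: about 15% at an ICC of 0.01 and 40% at 0.10 from the unrounded half-widths, or 13% and 38% from the rounded values (0.51/0.45 and 0.62/0.45). These use 10 degrees of freedom. If facility is fitted as a factor, 12 wards leave 12 − 2 − (facilities − 1), that is 7 with four facilities or 5 with six, and the multiplier rises from 2.23 to 2.36 or 2.57. Any facility variance removed by matching would partly offset this.

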## Ethics

3

In accordance with the relevant laws and regulations for studies with human subjects, the study has been approved by the Swedish Ethical Review Authority (Registration No. 2020–02046). One important aspect of the ethics pertaining to the study is the vulnerable nature of the individuals composing the study population. In addition to suffering from serious mental illness and being subject to strict regulation of everyday life, forensic mental health patients are also subject to various forms of stigma [38]. Thus, the study outlined in this article will take place in a context where power relations is an irrefutable and centrally influential feature of the milieu and the studied participants will be drawn from a population which is a highly marginalized group in society, often with limited ability to protect their own rights. From an ethical standpoint, these circumstances motivate an extra vigilant focus on ensuring that participating patients are informed of their rights as research participants and given ample opportunities to exercise them. In addition to participating patients, staff at the active wards will also be recruited to participate in the study for the purpose of answering the secondary objective pertaining to exploring experiences of working with the intervention. However, it seems highly reasonable to view staff participating in the study as less vulnerable than participating patients, given that the latter group will be comprised of persons with an anticipated low level of functioning that are also subject to highly restrictive state sanctioned limitations on autonomy and participation in society. Nevertheless, as in all studies, it will be important to inform staff approached for participation about their rights and the voluntary nature of research participation. In addition, we will ensure that staff are informed that the research team is independent from their employer.

The previously mentioned marginalized and stigmatized situation of the population of interest for this study, underscores the need to collect and store data in a judicious way. Data in a digital format will be encrypted and password protected. Physical copies such as completed questionnaires and consent forms will be stored in locked and secure conditions designed for storing research data securely (i.e. university facilities intended for this purpose). We will avoid collecting excessive and personal data, for instance by asking participants not to use their full name in any of the recordings of an IMR-session or during the S-NoMAD interviews.

In summary, ensuring and protecting the rights and interests of participating patients and staff is crucial. However, our estimation is that the measures described above minimize such risk. Given the almost non-existent evidence-base available in the forensic mental health field and the potential role of research in addressing important clinical issues, thus improving the care received by the individual patient, we argue that the benefits by far outweigh the potential risks.

## Discussion

4

The proposed study will investigate the effects of an evidenced-based treatment within a population of offenders with serious mental illness. Thus, it relates to the issue of translatability of interventions used in non-forensic mental health care to forensic populations, which has been highlighted as a research field of practical and theoretical importance [1]. As previously mentioned, more evidence-based interventions within the field of forensic mental health care are sorely needed. This point is given further pertinence when the severe suffering of the patient population and potentially large societal ramifications of treatment failure are considered. In exploring experiences of staff delivering the intervention, as well as investigating the potential role of moderating factors on treatment outcome, the proposed study also aims to address questions of central importance for health-care providers making treatment decisions and organizing treatment delivery for complex patients with competing clinical needs. However, the proposed project has some important limitations that we feel deserve mentioning.

Firstly, there are differences between how countries structure forensic mental health care and how mental illness is considered in different judicial systems. Thus, when considering the generalizability of the results of our study to another national context, differences in national jurisprudence and practice of forensic mental health delivery should be taken into account. Secondly, the practitioners delivering IMR in our study will, as mentioned, be forensic mental health nurses and auxiliary staff at the wards in our active condition. They may have limited previous experiences with delivering structured psychosocial interventions. Thus, it is plausible that better quality of treatment could be insured by assigning treatment delivery to staff with more experiences of group treatments, e.g. a licensed psychologist well versed in IMR-treatment. However, previous studies with IMR have employed a similar method of delivery, with regular staff serving as group leaders after receiving training in IMR [11,39,40]. Our experience is that this is the usual mode of delivery for psychosocial interventions when applied within inpatient settings. Thus, we consider this aspect of our design to be a part that strengthens the ecological validity of the study. Furthermore, we have tried to compensate for this potential weakness by providing clinical supervision and by inclusion of process measures within our design.

Lastly, we would have wished to be able to include a larger number of participants within our study, to ensure sufficient statistical power. In planning our study, we have found it necessary to balance a desire for sufficient sample size against practical considerations based on finite resources and environmental constraints. Thus, results from outcome measures will have to be interpreted and reported with caution. However, our proposed sample size is comparable or markedly larger than samples included in several previous studies of IMR [[16], [39], [40]]. It should also be noted that the current project is not solely concerned with treatment outcomes but also pertain to staff experiences of implementing and working with IMR, which can hopefully add to our understanding of interventions of this kind when applied in this context. We also hope that our study can stimulate further enquiry into the effectiveness of psychosocial interventions within the forensic mental health field and ideally support meta-analytical efforts within the area.

